## Abstract

**Background:**

We developed a smartphone app—the SUCCESS (Supporting Culturally and Linguistically Diverse CKD Patients to Engage in Shared Decision-Making Successfully) app—to support Australian adults with kidney failure undertaking dialysis to actively participate in self-management and decision-making. The content of the SUCCESS app was informed by a theoretical model of health literacy that recognizes the importance of reducing the complexity of health information as well as providing skills necessary to access, understand, and act on this information.

**Objective:**

The purpose of this study is to investigate the efficacy of the SUCCESS app intervention.

**Methods:**

We designed a multicenter pragmatic randomized controlled trial to compare the SUCCESS app plus usual care (intervention) to usual care alone (control). A total of 384 participants receiving in-center or home-based hemodialysis or peritoneal dialysis will be recruited from six local health districts in the Greater Sydney region, New South Wales, Australia. To avoid intervention contamination, a pragmatic randomization approach will be used for participants undergoing in-center dialysis, in which randomization will be based on the days they receive hemodialysis and by center (ie, Monday, Wednesday, and Friday or Tuesday, Thursday, and Saturday). Participants undergoing home-based dialysis will be individually randomized centrally using simple randomization and two stratification factors: language spoken at home and research site. Consenting participants will be invited to use the SUCCESS app for 12 months. The primary endpoints, which will be assessed after 3, 6, and 12 months of app usage, are health literacy skills, evaluated using the Health Literacy Questionnaire; decision self-efficacy, evaluated using the Decision Self-Efficacy Scale; and rates of unscheduled health encounters. Secondary outcomes include patient-reported outcomes (ie, quality of life, evaluated with the 5-level EQ-5D; knowledge; confidence; health behavior; and self-management) and clinical outcomes (ie, symptom burden, evaluated with the Palliative care Outcome Scale–Renal; nutritional status, evaluated with the Patient-Generated Subjective Global Assessment; and intradialytic weight gain). App engagement will be determined via app analytics. All analyses will be undertaken using an intention-to-treat approach comparing the intervention and usual care arms.

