### Design

The SUCCESS trial is a 12-month multicenter pragmatic RCT with a 1:1 allocation to two groups: SUCCESS app plus usual care versus usual care alone.

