#### Dialysis at Home

Participants will be randomized individually using minimization and two stratification factors: the language spoken at home and the research site. An interactive voice response system will be used for randomization; this allows for research staff to call a third party—the National Health Medical Research Council Clinical Trials Centre—which allocates the randomization order.

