**Baseline measurements**										
	Demographics: age, gender, country of birth, language spoken at home, Aboriginal and Torres Strait Islander status, and highest education attained.	✓^a^								
	Dialysis history: mode of dialysis (hemodialysis or peritoneal dialysis), location of treatment (home or in-center), dialysis schedule (frequency of dialysis per week), and dialysis vintage (years on dialysis).	✓								
	Cognition impairment: the MoCA^b^ is a screening tool developed to assist clinicians in the detection of cognitive impairment [20]. It measures a person’s orientation in time and space, short-term memory, abstract reasoning, attention, and many other aspects of cognitive ability. The MoCA tool was chosen as it is a more sensitive tool for detecting mild cognitive impairment compared to the MMSE^c^ [21]. The MoCA returns a cognitive ability score ranging from 0 to 30, where a score of ≤26 suggests cognitive impairment [20].	✓								
	Health literacy, self-report: the brief health literacy screener is a single-item screener to identify people with inadequate levels of functional health literacy in clinical settings [22,23]. The item asks, “How confident are you filling out medical forms by yourself?”; the item is rated on a 5-point response scale ranging from “not at all” to “extremely.” The threshold for inadequate health literacy is “somewhat” or less.	✓								
	Health literacy, performance-based: a brief comprehension test based on instructions similar to those found on a packet of aspirin bought over the counter [24]. Participants are asked to read a fictitious medicine label and respond to four questions, such as “What is the maximum number of days you may take this medicine?” and “List one condition for which you might take the tablet.” The task was developed according to a conceptual framework that defines literacy as an ability to fulfill goal-directed tasks, in this case, in a health context. Health literacy is categorized as high (maximum score), medium (one error), or low (more than one error).	✓								

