### Data Analysis

#### Overview

Analysis of data will occur using an intention-to-treat approach and will compare the intervention and usual care arms. For continuous and binary outcomes, linear and logistic regression models will be used, respectively, with study arm as a covariate. All models will also be adjusted for center using a random effect, and the type of patient (ie, receiving home-based or in-center care) will be adjusted for using a covariate.

Qualitative data will be analyzed using the Framework approach to thematic analysis [31]. Framework analysis is a matrix-based approach with columns depicting themes and rows listing the cases, enabling the relationship between themes and cases to be explored. The first step involves familiarization with the data, where one or two researchers will review the transcript and, using an inductive approach, they will then develop a list of emerging topics and salient themes. These initial impressions will form the basis of the coding framework. Then, additional researchers will independently read a subset of transcripts and review the framework, which will further be revised with continuous discussion if needed. One researcher will then code all the interviews into the final framework, of which a random subset (10%) will be double coded by an additional researcher to ensure rigor. Similarities or differences will be discussed and reassessed. Microsoft Excel will be used to summarize the themes and supporting quotes from each transcript in the framework. Prominent themes arising from the framework will be identified and discussed in-depth with the research team.

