### Sample Size

Our sample size has been calculated based on the primary outcome of the three Health Literacy Questionnaire (HLQ) domains. We assumed a minimal clinically important difference of 0.25 units in any one of the three HLQ domains. A sample size of 384 participants would result in greater than 90% power to detect a 0.25-unit change in an HLQ domain between the two arms, assuming an SD of 0.60, and at least 80% power, assuming an SD of 0.75. These SD values are based on published literature and equate to a standardized difference of 0.42 and 0.33, respectively; a standardized difference of 0.5 is considered a medium effect [33,34]. Our power calculation is based on conducting our analyses using 2-sided tests, a 5% significance level, and assuming 20% loss to follow-up (eg, due to death or kidney transplant).

For qualitative interviews, a maximum total sample size of 40 participants is planned. Interviews will continue until data saturation or until the maximum total sample size is reached.

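### Home-dialysis allocation is described both as simple randomization and as minimization, and the stated outcome model leaves out language spoken at home, one of the two balancing factors

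*Protocol article*

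**What the plan says.** On allocation of home-dialysis participants, the Protocol article speaks twice.

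- Abstract, Methods paragraph: they are "individually randomized centrally using simple randomization and two stratification factors: language spoken at home and research site".
- Methods, Randomization, Dialysis at Home: "Participants will be randomized individually using minimization and two stratification factors: the language spoken at home and the research site". The same paragraph adds that a third-party trials center issues the allocation through a voice response system.

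On the analysis, Data Analysis, Overview, states that for continuous and binary outcomes "linear and logistic regression models will be used, respectively, with study arm as a covariate". It continues: "All models will also be adjusted for center using a random effect, and the type of patient" is also accounted for, in that "the type of patient (ie, receiving home-based or in-center care) will be adjusted for using a covariate". Language spoken at home is not among the adjustment terms.

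Language is available for the model. Table 1 lists it among the baseline items: "Demographics: age, gender, country of birth, language spoken at home".

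**The concern.** There are two linked problems.

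First, simple randomization and minimization are different procedures. Simple randomization ignores all participant characteristics, so the Abstract disagrees with itself as well as with Methods. A reader cannot tell which procedure produced the home-dialysis arms, and so cannot tell which analysis respects it.

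Second, if minimization was run, language was forced close to balance between the arms among home participants. A model that omits a balanced prognostic factor leaves that factor's variance in the residual and computes a standard error as if the factor could differ freely between arms. The standard error is then too large. Choosing language as a balancing factor suggests that the investigators expect it to be prognostic. The app is also aimed at culturally and linguistically diverse patients, so language is a natural candidate to matter for health literacy.

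What is at stake is a clear account of the allocation and some precision in the primary comparisons.

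**Working it through.** **1. The plan's own power figure.** Sample Size states that "A sample size of 384 participants would result in greater than 90% power to detect a 0.25-unit change in an HLQ domain" at SD 0.60, and at least 80% at SD 0.75, with two-sided 5% tests and 20% loss. Allocation is planned "with a 1:1 allocation to two groups", so n = 384 × 0.8 / 2 = 153.6 per arm.

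- Standardized differences: 0.25/0.60 = 0.417 and 0.25/0.75 = 0.333, matching the stated 0.42 and 0.33.
- Power, taking participants as independent: 95.5% at SD 0.60 and 83.2% at SD 0.75. Both statements reproduce. Nothing in this point disputes them.

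**2. Does the choice of method matter in practice?** This was simulated under assumed inputs: 40% of home participants speak another language, there are 6 sites, and minimization uses a biased coin of 0.8. The figures are the absolute between-arm difference in the number of other-language speakers.

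| Home participants | Simple: mean (95th percentile) | Minimization: mean (95th percentile) |
|---|---|---|
| 60 | 4.0 (10) | 1.0 (3) |
| 100 | 5.1 (13) | 1.1 (3) |
| 150 | 6.1 (15) | 1.1 (3) |

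As a check on the second row, about 40 such participants allocated by coin toss give a mean of about √(2 × 40/π) = 5.0. The two descriptions therefore imply visibly different balance.

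**3. Model against allocation.** Minimization factors: language and research site. Model terms: arm, center (random effect) and patient type. Site is covered if center and research site are the same unit. Language is not covered.

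**4. Size of the test when language is omitted.** Let h be the home share and R² the share of outcome variance explained by language. Take language as perfectly balanced among home participants and as varying freely among in-center participants. The true variance of the arm difference is then (1 − h·R²) times the variance that the model assumes, and

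true size = 2 × [1 − Φ(1.96 / √(1 − h·R²))].

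| h | R² | 1 − h·R² | True size | Power at SD 0.75, language omitted | Power at SD 0.75, language included |
|---|---|---|---|---|---|
| 0.3 | 0.05 | 0.985 | 4.8% | 83.4% | 85.0% |
| 0.3 | 0.10 | 0.970 | 4.7% | 83.5% | 86.8% |
| 0.5 | 0.05 | 0.975 | 4.7% | 83.5% | 85.0% |
| 0.5 | 0.10 | 0.950 | 4.4% | 83.8% | 86.8% |

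For power, the standard error is 0.75 × √(2/153.6) = 0.0856 and 0.25/0.0856 = 2.92. With language omitted, power = Φ((2.92 − 1.96)/√(1 − h·R²)). With language included, power = Φ(2.92/√(1 − R²) − 1.96).

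The gain of 1.5 to 3.3 percentage points is at the favorable end. It credits in-center participants with the same variance reduction and ignores what the center term already absorbs. Both h and R² are assumptions, and perfect balance is a limit that minimization only approaches.

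**The case against.** The strongest reply is that the Abstract wording is a slip. Both places agree on individual, central allocation and on the same two factors, and Methods carries the operational detail. That is largely right: on its own, this half is close to a clerical correction. It still needs confirming, because if plain simple randomization was in fact run, omitting language would not make the test conservative, and language would be only an optional prognostic covariate.

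A second reply is that the article condenses a fuller plan, and an unseen SAP may add the balancing factors. This weakens the point without removing it. The article is not silent here: it gives an adjustment set and applies it to all models.

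Three stronger readings are tempting, and the documents do not support them.

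- **Bias or inflated type I error.** Omitting a balanced factor works in the conservative direction.
- **A true size of 4.4% to 3.9%.** That is the formula at h = 1 with R² of 5% and 10%. It describes an analysis of home participants alone, and the plan pools them with in-center participants.
- **Serious uncorrected language imbalance among in-center participants.** Each center supplies both arms through its two attendance patterns, so differences in language mix between centers are largely handled by the design and the center term. What remains is ordinary chance imbalance. The documents give no figure for how much variance language would remove there. Entry also requires enough English to consent, which may narrow the effect of home language.

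**Conclusion.** The contradiction in the allocation method is certain from the text. The omission of language from the stated model is explicit. The statistical consequence is modest: if minimization was run, a nominal 5% test in the pooled analysis has a true size of about 4.8% to 4.4%, for an assumed R² of 5-10% and an assumed home share of 30-50%. This is a small loss of precision with no bias. Over that range the calculated power at SD 0.75 stays above the stated 80% even without language.

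The result rests on a normal approximation, on near-perfect balance of language among home participants, and on language explaining variance beyond center and patient type. It takes no account of allocation by attendance pattern among in-center participants, which is a separate matter. The change is worth making because it is cheap and brings the model into line with the design.

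**What to change.** 1. Confirm with the central allocation service which procedure was run for home-dialysis participants, and state that one procedure in both the Abstract and Dialysis at Home.
2. In Data Analysis, Overview, add language spoken at home as a fixed covariate in all outcome models, alongside center and patient type. Code it as it was coded for the minimization; the article does not give that coding. Record the change before the outcome data are analyzed.

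The cost is small but not nil. No new data are needed and the sample size does not change. The covariate uses about one degree of freedom if language has two categories. A very small category or missing entries would need a handling rule. For binary outcomes the odds ratio becomes conditional on language, which the text should say.

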**Results:**

The study has been approved by Nepean Blue Mountains Human Research Ethics Committee (2020/ETH00910) and recruitment has begun at nine sites. We expect to finalize data collection by 2023 and publish the manuscript by 2024.

**Conclusions:**

Enhancing health literacy skills for patients undergoing hemodialysis is an important endeavor, given the association between poor health literacy and poor health outcomes, especially among culturally diverse groups. The findings from this trial will be published in peer-reviewed journals and disseminated at conferences, and updates will be shared with partners, including participating local health districts, Kidney Health Australia, and consumers. The SUCCESS app will continue to be available to all participants following trial completion.

**Trial Registration:**

Australia New Zealand Clinical Trials Registry (ANZCTR) ACTRN12621000235808; https://www.anzctr.org.au/Trial/Registration/TrialReview.aspx?id=380754&isReview=true

**International Registered Report Identifier (IRRID):**

DERR1-10.2196/39909

## Introduction

Chronic kidney disease (CKD) affects up to 10% of the Australian population [1], with greater prevalence, higher mortality, and more rapid disease progression in culturally and linguistically diverse communities [2]. The long-term management of CKD is complex, requiring patient involvement both in decision-making and self-management. Effective self-management and health decision-making requires the ability to understand and use health information, a skill that is known as “health literacy” [3]. However, limited health literacy is common in CKD populations [4] and is independently associated with missed dialysis treatments, increased emergency department visits, increased mortality, and poorer quality of life [5,6]. This is further compounded by the fact that cognitive impairment is more prevalent in those undertaking dialysis compared to the general population, with deficits in attention, memory, and executive function [7]. These cognitive deficits may impact cognitive processing, speed, memory, and the ability to plan ahead and strategize—all necessary skills for participating in self-management and decision-making.

Interventions that focus on developing health literacy skills may have positive effects on shared decision-making and self-management for people living with chronic diseases [8]. In people with CKD, there is mounting evidence that health literacy interventions may increase kidney disease–related knowledge, improve self-care behaviors and self-efficacy, and decrease hospitalization rates and length of stay [9]. However, a recent systematic review highlighted that the quality of the evidence is low and that no studies have specifically targeted populations with low health literacy [9]. The authors concluded that future studies should use validated measures of health literacy and determine whether health literacy interventions redress inequity and, specifically, whether these interventions are more beneficial in those with low health literacy [9].

Health literacy interventions may take several forms, such as educational methods varying from formal classes, home visits, and study circles, through to multimedia and eHealth or online interventions [9,10]. eHealth interventions are potentially useful methods to deliver health literacy interventions. It is estimated that over 91% of Australians own a smartphone, and smartphones are used to access information more than any other devices [11]. Furthermore, smartphone interventions can reduce the cognitive burden placed on users by providing small unit-based learning called “microlearning,” allowing users to return to the content at their own pace and in their own time. eHealth interventions have been shown in different settings to provide consumers access to relevant health information, enhance quality of care, and encourage behavior change [12]. Several CKD-related apps already exist; however, current evidence suggests that many CKD-related apps lack accurate, evidence-based information [13], and none are designed based on theoretical models to improve health literacy.

We recently developed a smartphone app—the SUCCESS (Supporting Culturally and Linguistically Diverse CKD Patients to Engage in Shared Decision-Making Successfully) app—to support Australian adults with kidney failure to actively participate in self-management and decision-making [14]. The SUCCESS app was developed with a multidisciplinary team that included researchers in various fields (ie, health literacy, shared decision-making, public health, epidemiology, and computer science), renal clinicians (ie, nephrologists, dietitians, physiotherapists, and social workers), and consumers living with kidney failure. Content was informed by a theoretical model of health literacy [15] that recognizes the importance of reducing the complexity of health information as well as supporting consumers to develop their skills and to access, understand, and act on this information. In this way, it adopts strategies to reduce the complexity of the content (ie, diet, fluids, medicine, physical activity, emotional well-being, and supportive care) and includes features to improve the health literacy skills of patients. The latter includes question prompt lists and evidence-based volitional help sheets to support question-asking and behavioral change as well as animated skills training related to communication, shared decision-making, and critical appraisal of health information. Full details of the development and content of the app have been published elsewhere [14].

The purpose of this randomized controlled trial (RCT) is to investigate the efficacy of the SUCCESS app intervention for adults receiving in-center hemodialysis, home-based hemodialysis, or peritoneal dialysis, including those from culturally and linguistically diverse backgrounds and with lower health literacy. Our objectives are to assess the impact of the SUCCESS app on the primary outcomes, including health literacy skills, decision self-efficacy, and rates of unscheduled health encounters, and on the secondary outcomes, including knowledge, confidence, quality of life, symptom burden, and nutritional status.

## Methods

### Overview

The study methods have been informed by a feasibility study of the intervention [16]. This protocol is reported in accordance with the SPIRIT (Standard Protocol Items: Recommendations for Interventional Trials) guidelines and the CONSORT (Consolidated Standards of Reporting Trials) guidelines [17]. The trial was registered on the Australia New Zealand Clinical Trials Registry (ACTRN12621000235808).

### Design

The SUCCESS trial is a 12-month multicenter pragmatic RCT with a 1:1 allocation to two groups: SUCCESS app plus usual care versus usual care alone.

### Intervention

#### Intervention Development

The SUCCESS app was designed using strategies to reduce the complexity of the content as well as to include features to improve the health literacy skills of patients. The app embeds informational content relevant to living with kidney failure covering diet, fluids, medicine, physical activity, emotional well-being, and supportive care [14]. A four-step process was used to simplify written content, including calculating readability statistics, applying the Patient Education Materials Assessment Tool [18], supplementing written information with video and audio content, and incorporating microlearning and interactive quizzes.

The app also includes features to improve the communicative and critical health literacy skills of patients across four domains: skills to (1) access, (2) understand, (3) appraise, and (4) use health information to make health decisions and be involved in self-management. This is achieved through the inclusion of question prompt lists, volitional help sheets, and animated skills training in communication, shared decision-making, and critical appraisal of online information (Textbox 1). The SUCCESS app is designed for use on both iOS and Android platforms.

Features of the SUCCESS app.
